### Recruitment {15}

Patients who are scheduled to undergo minimally invasive gastric or colorectal cancer surgery will be considered as candidates for trial enrolment in concordance with the inclusion and exclusion criteria. Informed consent will be obtained from all participants by investigators. We are confident that we can enroll a sufficient number of eligible patients, as our institution conducts over 150 surgeries for gastric cancer and 300 surgeries for colorectal cancer annually.

## Assignment of interventions: allocation

### Sequence generation {16a}

Eligible patients will be randomly allocated to use absorbable barbed or monofilament sutures for midline fascia closure in a 1:1 ratio. Stratified randomization was performed by medical statisticians who do not participate in this study. This randomization is based on an independent, computer-based sequence generated from the implementation of the dynamic algorithm with the cancer types as the stratifying variables.

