### Sample size {14}

We mainly have used absorbable monofilament sutures for fascia closure, and the overall incidence of incisional hernia was about 15%. Barbed suture began to be used for fascial closure in August 2020 during colorectal surgery. Before this randomized controlled trial, we conducted a pilot study of barbed suture for fascia closure. A total of 60 patients underwent fascia closure with barbed suture during laparoscopic colorectal surgery, and incisional hernia occurred in 2 patients (3.3%) within 1 year after surgery. Assuming additional patients with an incisional hernia during follow-up period, we determined possible incisional hernia rate to 5% in the barbed suture group for 3 years after surgery. Therefore, we hypothesized that the incidence of incisional hernia at 3 years after surgery will be lower in the barbed suture group than in the monofilament suture group. The sample size was calculated on the basis of this analysis plan, assuming that the incisional hernia rate of the barbed suture and monofilament groups at 3 years after surgery will be 5% and 15%, respectively. We calculated that 141 patients per group needed to achieve a two-sided α of 0.05 and statistical power of 80% using a chi-squared test. Assuming a 10% dropout rate, it is necessary to recruit 312 patients. Finally, 156 patients were assigned to the barbed suture and monofilament groups. The calculations were performed using G*Power 3.1.

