## Statistical methods

### Statistical methods for primary and secondary outcomes {20a}

A planned analysis will be performed after all patients have completed their 3-year follow-up. Categorical variables will be presented as numbers with percentages, and continuous variables will be presented as means with standard deviations or medians with interquartile ranges. The analysis will be performed using the intention-to-treat approach. The primary outcome will be analyzed using chi-squared and Kaplan-Meier tests. Risk factors for incisional hernia will be analyzed using the Cox regression analysis. Secondary outcomes will be tested using the chi-squared test for categorical variables and the *t*-test or Mann-Whitney test for continuous variables, as appropriate. The level of statistical significance will be set at *p* < 0.05.

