### Method for additional analyses (e.g., subgroup analyses) {20b}

Subgroup analyses will be performed on the type of cancer (gastric or colorectal cancer). Values of *p* < 0.05 will be considered statistically significant.

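### Allocation is stratified by cancer type but the named primary tests have no stratum term, so they may be slightly conservative: a minor, almost free improvement

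*Protocol article*

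**What the plan says.** Sequence generation {16a} sets 1:1 allocation, with the sequence "generated from the implementation of the dynamic algorithm with the cancer types as the stratifying variables". Implementation {16c} again describes the list as stratified.

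Statistical methods {20a} fixes the primary comparison in one sentence: "The primary outcome will be analyzed using chi-squared and Kaplan-Meier tests". It names no stratum or covariate. Sample size {14} rests on the same plain test: "We calculated that 141 patients per group needed to achieve a two-sided α of 0.05 and statistical power of 80% using a chi-squared test".

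Two other analyses bear on the point. In {20a}, "Risk factors for incisional hernia will be analyzed using the Cox regression analysis"; the covariates are not listed, and this model is not presented as the treatment comparison. In {20b}, cancer type returns as a subgroup factor: "Subgroup analyses will be performed on the type of cancer (gastric or colorectal cancer").

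**The concern.** When allocation is balanced within cancer types, differences in hernia risk between the cancers cannot add to the variance of the treatment difference. A plain chi-squared or log-rank test still counts that between-cancer variation as noise. If the two cancers carry different risks, its standard error is therefore somewhat too large, its p-value somewhat too high and its confidence interval somewhat too wide.

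What is at stake is a little efficiency in a trial sized at 80% power. Equal risk in the two cancers cannot be taken for granted. The pilot behind the 5% barbed rate (2 hernias in 60 patients) was in colorectal surgery only, and the article reports no barbed-suture result for gastric surgery.

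**Working it through.** **Inputs from the article**
- Two-sided α 0.05, 80% power, 141 per group, 1:1 allocation ({14}, {16a}).
- Three-year hernia rates of 5% (barbed) and 15% (monofilament) ({14}).
- 10% dropout, 312 patients in total ({14}).
- Visits at 6, 12, 18, 24 and 36 months (Primary outcome).

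**Assumptions, because the article does not give them**
- Hernia rates by cancer type: several pairs were tried.
- Cancer mix: 2:1 colorectal to gastric, borrowed from the annual volumes of 300 and 150 in Recruitment {15}. A 1:1 mix was also tried.
- Exact balance between arms within each cancer.
- The time-to-event test is a log-rank test (Kaplan-Meier is an estimator, so the article does not identify the test).

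**Step 1: the plan's own figure**

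Pooled-variance formula, no continuity correction:

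n = [1.96·√(2·0.10·0.90) + 0.8416·√(0.15·0.85 + 0.05·0.95)]² / 0.10² = (0.8316 + 0.3521)² / 0.01 ≈ 140.1, rounded up to 141.

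The stated 141 is reproduced, with power 80.3%. For dropout, 141 × 1.1 = 155.1 gives 156 per group and 312 in total. Dividing by 0.9 would give 157 and 314, a difference of no consequence here. The plan's figure is thus that of an unstratified chi-squared test.

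**Step 2: direction and size by formula**

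Let w be the colorectal share, pC and pG the null rates in the two cancers, and p̄ = w·pC + (1−w)·pG.
- Variance the plain test assumes is proportional to p̄(1−p̄).
- True variance under balance is proportional to w·pC(1−pC) + (1−w)·pG(1−pG).
- The first exceeds the second by w(1−w)(pC−pG)², which is never negative.

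With r the ratio of true to assumed variance, the true size is 2·[1 − Φ(1.96/√r)]. Since r ≤ 1, the size cannot exceed 5%.

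Example with 20%/5% and a 2:1 mix:
- p̄ = 0.15 and p̄(1−p̄) = 0.1275.
- True variance term = (2/3)(0.16) + (1/3)(0.0475) = 0.1225.
- r = 0.1225/0.1275 = 0.961, so 1.96/√r = 2.00 and the size is 4.55%.
- The standard error is overstated by 1/√0.961 = 1.02, or about 2%.

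**Step 3: simulated type I error, chi-squared against Cochran-Mantel-Haenszel (CMH)**

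282 patients with outcomes, 400,000 runs per row:

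| Colorectal/gastric rate | Mix | Plain chi-squared | CMH |
|---|---|---|---|
| 15%/15% | 2:1 | 5.05% | 5.05% |
| 17.5%/10% | 2:1 | 4.94% | 5.00% |
| 20%/5% | 2:1 | 4.55% | 4.95% |
| 25%/5% | 2:1 | 4.38% | 5.04% |
| 17.5%/10% | 1:1 | 4.89% | 4.95% |
| 20%/5% | 1:1 | 4.42% | 4.96% |
| 25%/5% | 1:1 | 4.18% | 4.96% |

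**Step 4: log-rank**

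312 patients, 2:1 mix, detection at the planned visits, 10% dropout, 8,000 runs, unstratified against stratified: 4.8% and 4.8% at 15%/15%; 4.5% and 5.0% at 20%/5%; 4.3% and 5.1% at 25%/5%. Simulation error is about √(0.05·0.95/8000) = 0.24 points, so this supports the direction more than the exact size.

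**Step 5: power**

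Design odds ratio (0.05/0.95)/(0.15/0.85) = 0.298, 2:1 mix, 282 patients:

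| Control rates (colorectal/gastric) | Plain chi-squared | CMH | Difference |
|---|---|---|---|
| 17.5%/10% | 81.5% | 81.9% | 0.3 points (81.51 to 81.85) |
| 20%/5% | 80.6% | 81.7% | 1.1 points (80.63 to 81.70) |
| 25%/5% | 87.3% | 88.2% | 0.8 points (87.32 to 88.16) |

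Power was not simulated for the 1:1 mix.

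**The case against.** The strongest reply is that a journal article names families of tests and leaves their stratified form to an analysis plan, which is not shown here. The article never says that the strata will be ignored, and its sample size and analysis sections agree with each other. That stands in part: this is not a contradiction or an error. But the article does name the primary test and sizes the trial on its plain form, so a stratified analysis would refine what is published rather than fill a blank.

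A reader might infer that error rates are compromised. They are not: the departure runs only towards too few rejections.

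A reader might also look for a large effect. One can be produced. Rates of 5% colorectal and 35% gastric with a 2:1 mix, and 156 evaluable per arm, bring the plain test down to 3.2%. Rates of 30%/3% give 3.9% (2:1) or 3.5% (1:1) by the Step 2 formula. Nothing in the article supports such gaps; it gives only an overall incidence of about 15%.

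Nor can it be said that the stratification goes unused. It secures balance on cancer type whatever test follows, and it directly helps the planned subgroup analysis. Cancer type may also enter the risk-factor Cox model. Finally, the dynamic algorithm is not described in detail. Imperfect balance within strata would bring the plain test closer to 5% and shrink the effect further.

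**Conclusion.** The point holds as a minor efficiency improvement. The design stratifies on cancer type, and no stated whole-population treatment comparison uses it. Under the assumed rates from 17.5%/10% to 25%/5%, the plain chi-squared test has a true type I error of about 4.2% to 4.9%, and loses about 0.3 to 1.1 points of power at a 2:1 mix. With equal rates the effect disappears. These figures depend on assumed stratum rates, an assumed mix and near-exact balance. The direction (conservative) depends only on within-stratum balance and differing risks. Neither the 312-patient sample size nor the credibility of a positive result is threatened.

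**What to change.** In Statistical methods {20a}, state that the primary comparison is stratified by cancer type: a Cochran-Mantel-Haenszel test for the 3-year proportion and a stratified log-rank test for time to hernia. Report the treatment effect with a 95% CI from a Cox model stratified by cancer type, kept separate from the risk-factor model.

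No extra patients, visits or data are needed, since cancer type is already known for everyone at randomisation. If the risks prove equal, the stratified test gives up essentially nothing (5.05% for both tests at 15%/15%). The sample size can stay as it is. The cost is a protocol amendment, which under {25} means ethics review and an updated registry entry and protocol. Because the investigators know the allocation ({17b}), it should be dated before any comparison of hernia by arm. If an existing analysis plan already specifies the stratified tests, aligning the published sentence with it is enough.

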### Concealment mechanism {16b}

To achieve randomization, a computer-generated sequence methodology will be used, which will ensure that both the randomization methodology and the allocation sequence are concealed from both the investigator and the participants.

### Implementation {16c}

An independent medical statistician will generate a stratified randomization list for allocation sequence. Investigators will enroll and assign participants to interventions.

## Assignment of interventions: blinding

### Who will be blinded {17a}

After the interventions are assigned, participants will be blinded. The results will be kept confidential from the participants throughout the entire trial. Surgeons will not be blinded because the intervention involves a surgical procedure.

### Procedure for unblinding if needed {17b}

As investigators are aware of the participant allocation, unblinding would not be required.

## Data collection and management

### Plans to promote participant retention and complete follow-up {18b}

Participants are patients with gastric or colorectal cancer who require regular follow-up to evaluate cancer recurrence. We expect that participants will be available for follow-up due to concerns of cancer recurrence.

### Data management {19}

The study data will be collected and recorded electronically, and stored securely on computers and hard drives. Only the investigators will have access to the participants’ files, and they will be the only ones authorized to make changes to the information. This will ensure that the data remains accurate and validated throughout the study.

### Confidentiality {27}

Datasets will be anonymized, and only summary data, which cannot identify individual participants, will be presented in the manuscript.

### Plans for collection, laboratory evaluation, and storage of biological specimens for genetic or molecular analysis in this trial/future use {33}

Not applicable as no biological specimens were collected in this study.

## Statistical methods

### Statistical methods for primary and secondary outcomes {20a}

A planned analysis will be performed after all patients have completed their 3-year follow-up. Categorical variables will be presented as numbers with percentages, and continuous variables will be presented as means with standard deviations or medians with interquartile ranges. The analysis will be performed using the intention-to-treat approach. The primary outcome will be analyzed using chi-squared and Kaplan-Meier tests. Risk factors for incisional hernia will be analyzed using the Cox regression analysis. Secondary outcomes will be tested using the chi-squared test for categorical variables and the *t*-test or Mann-Whitney test for continuous variables, as appropriate. The level of statistical significance will be set at *p* < 0.05.

### Interim analyses {21b}

We have no plans to conduct any interim analyses, since both interventions have low risk.

### Method for additional analyses (e.g., subgroup analyses) {20b}

Subgroup analyses will be performed on the type of cancer (gastric or colorectal cancer). Values of *p* < 0.05 will be considered statistically significant.

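### The p < 0.05 rule for the cancer-type subgroups, applied with the tests the article names, does not test whether the suture effect differs between gastric and colorectal cancer

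*Protocol article*

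**What the plan says.** The section on additional analyses (20b) has two sentences: "Subgroup analyses will be performed on the type of cancer (gastric or colorectal cancer). Values of" *p* < 0.05 are then declared significant. It names no test.

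The between-arm tests appear under Statistical methods (20a). For the primary outcome, "The primary outcome will be analyzed using chi-squared and Kaplan-Meier tests". Secondary outcomes get the chi-squared test, the t-test or the Mann-Whitney test. Cox regression is named only for the analysis of risk factors. A significance level of 0.05 is already set there for the main analyses.

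The Sample size section (14) assumes an "incisional hernia rate of the barbed suture and monofilament groups at 3 years after surgery will be 5% and 15%, respectively", and finds "141 patients per group needed to achieve a two-sided α of 0.05 and statistical power of 80% using a chi-squared test". That power is for the whole sample. No power or expected size is given by cancer type. Cancer type is the stratification factor for randomisation (16a). The only information on case mix is under Recruitment (15): "our institution conducts over 150 surgeries for gastric cancer and 300 surgeries for colorectal cancer annually".

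**The concern.** The useful question for a subgroup analysis is whether the treatment effect depends on cancer type. A chi-squared or Kaplan-Meier comparison within one cancer asks something else, namely whether the arms differ in that cancer. When two such tests disagree, the disagreement may only reflect that one subgroup is smaller.

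The trial is sized to give 80% power with all patients together, so each subgroup is clearly underpowered and disagreement between the two p-values is to be expected even when the effect is the same in both. A reader of the results could take such a split as evidence about which patients benefit from barbed suture. The smaller cancer group would tend to be the one that appears not to benefit, simply because it is smaller.

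**Working it through.** **Inputs.** From Sample size (14): 15% and 5%, two-sided α 0.05, 80% power, 141 per arm, and 156 per arm after a 10% dropout allowance. From Sequence generation (16a): 1:1 allocation. The gastric share is not stated. Annual volumes of over 150 and 300 (Recruitment, 15) suggest 150/450 = 1/3, so 47 gastric and 94 colorectal evaluable patients per arm. Because this is an assumption, shares from 20% to 50% were also run.

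**The plan's own figure.** With mean rate 0.10:

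n = [1.960·√(2·0.10·0.90) + 0.842·√(0.15·0.85 + 0.05·0.95)]² / 0.10² = [0.8315 + 0.3521]² / 0.01 ≈ 140.1, so 141 per group. The stated figure reproduces.

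**Power within each cancer, same 15% vs 5% in both.** Power = Φ{[0.10·√n − 0.8315] / 0.4183}.

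- Gastric, n = 47: Φ(−0.349) = 0.364
- Colorectal, n = 94: Φ(0.330) = 0.629

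Exact binomial enumeration of the Pearson chi-squared test gives 0.401 and 0.653.

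**Chance that exactly one subgroup is significant.** The subgroups contain different patients, so P = pG(1 − pC) + pC(1 − pG).

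- Normal approximation: 0.364·0.371 + 0.629·0.636 = 0.535
- Exact: 0.401·0.347 + 0.653·0.599 = 0.530

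**Range over the unknown split** (exact, 141 evaluable per arm):

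| Gastric share | n per arm, gastric / colorectal | Power, gastric / colorectal | Exactly one significant |
|---|---|---|---|
| 20% | 28 / 113 | 0.244 / 0.739 | 0.622 |
| 25% | 35 / 106 | 0.309 / 0.710 | 0.580 |
| 33% | 47 / 94 | 0.401 / 0.653 | 0.530 |
| 40% | 56 / 85 | 0.432 / 0.603 | 0.514 |
| 50% | 70 / 71 | 0.524 / 0.530 | 0.499 |

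With all 156 per arm evaluable, the same calculation gives 0.540 at a one-third share, 0.624 at 20% and 0.490 at 50%.

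**Which way the split falls.** In 1,000,000 simulated trials at 47/94 per arm, only colorectal was significant in 39% and only gastric in 14%. Among trials with a significant overall result, the split occurred in about 60%.

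**No effect in either cancer.** Two independent tests at 0.05 give a nominal chance of at least one significant result of 1 − 0.95² = 0.0975.

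**An interaction test in the same setting.** In the simulations with the uniform 15% vs 5% effect, a Wald test comparing the two log odds ratios (0.5 added to each cell) rejected in 2.3% to 2.5% of trials. This is below the nominal 5% because the test is conservative with few events.

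**Sparse cells.** The expected number of barbed-arm gastric hernias at 47 patients is 47·0.05 = 2.35. The chance of none is 0.95⁴⁷ ≈ 0.09. In those trials an ordinary Cox or logistic interaction estimate would not be finite.

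**The case against.** The strongest reply is that section 20b never says each subgroup is tested separately. Its second sentence repeats the general significance level of section 20a and would fit an interaction test equally well. A journal article condenses a fuller protocol, which section 31c says is available on request, and the subgroup test could be specified there or in an analysis plan. The design is also restrained: one factor, two levels, named in the protocol article and identical to the randomisation stratum.

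Part of this stands. Separate testing is inferred, and the absence of an interaction test would not by itself be a finding in an article of this kind. But section 20b does attach a significance threshold to the subgroup analyses, and none of the between-arm tests the article names compares effects between cancers. Cox regression could carry a treatment-by-cancer term, but the article assigns it only to risk factors. Followed as written, the text yields one p-value per cancer. Stratifying by cancer type helps balance within subgroups but does not replace a test of difference.

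Two stronger inferences are tempting and not supported. A reader might infer that the trial intends to announce benefit in one cancer and not the other. No section plans such a claim; the objective, hypothesis, sample size and discussion all concern the overall comparison. A reader might also infer that a significant subgroup could rescue a failed primary test. The subgroup work is placed under additional analyses, and no subgroup endpoint is listed among the outcomes.

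**Conclusion.** The point holds in a limited form. The threshold in section 20b, applied with the tests the article names, would not answer the subgroup question and would often give discordant p-values under a uniform effect: about 50% to 62% of trials with 141 evaluable per arm, and 53% at the one-third gastric share.

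The assumptions are the protocol's own 15% and 5% in both cancers, a chi-squared test in each, and a gastric share between 20% and 50%. The one-third share comes from overall surgical volumes. Exclusions such as stoma formation, earlier abdominal surgery and off-midline incisions could shift it, so the range matters more than the single figure.

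The percentages count split p-values. They do not say how often a misleading conclusion would be published, and the 2.3% to 2.5% rejection rate of the interaction test is therefore not a like-for-like comparator. The matter is confined to a supporting analysis and is worth correcting because the correction is cheap.

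**What to change.** In section 20b, replace the subgroup significance rule with three statements.

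1. Whether the effect differs by cancer type will be assessed by one treatment-by-cancer-type interaction test, using a named method that tolerates sparse or zero cells. Options are Firth-penalised Cox or logistic regression, or an exact test of homogeneity of odds ratios.
2. The effect in each cancer will be reported with its 95% confidence interval.
3. The subgroup results are exploratory, the interaction test has low power, and a non-significant interaction is not evidence that the effects are equal.

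If the full protocol or analysis plan already contains such a test, it is enough to bring the article's wording into line with it.

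The cost is a few sentences. Cancer type is already recorded as the stratification factor, so no new data and no change to the design or sample size are needed. The price is the low power of the interaction test: the trial will be able to detect only a large difference between cancers.

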### Methods in the analysis to handle protocol nonadherence and any statistical methods to handle missing data {20c}

Loss to follow-up will be minimized due to the characteristics of cancer patients. If missing data is exceed 5% of any variable, multiple imputations will be used to handle missing values.

### Plans to give access to the full protocol, participant-level data, and statistical code {31c}

The full protocol and final datasets will be available from the corresponding author on reasonable request.

## Oversight and monitoring

### Composition of the coordinating center and trial steering committee {5d}

The authors will coordinate and steer this study.

